### Variables: operative definition

The main variable to be assessed in this study is time on INR therapeutic levels in the last 6 months of receiving VKA treatment. Appropriate INR level control will be assessed in two ways: measuring the therapeutic INR value percentages or time percentages in therapeutic values estimated using the Rosendaal method. It records the figure percentages as defined by their acceptable values according to the pathology the patient suffers from. This is from 2 to 3 for atrial fibrillation or from 2.5 to 3.5 if thromboembolism prevention is carried out after a heart valve surgery has been performed. Therefore, this quantitative variable had to be measured to calculate the patient’s percentage of an appropriate range, according to the patient’s condition.

Independent variables, also called study variables, are those that could affect the result variables. We classified them into eight groups to make their analysis easier.

Sociodemographic: age and sex, marital status, employment situation, and social and family support.

Somatometry and vital signs: height, weight, body mass index (BMI), diastolic and systolic blood pressure, and heart rate.

Cardiovascular risk factors: smoking habit, diabetes, arterial hypertension, dyslipidemia, and chronic renal failure.

Cardiovascular conditions: atrial fibrillation (AF), interventional cardiac valve diseases with or without AF, ischemic cardiopathy, thromboembolic disease history (stroke, transient ischemic attack), hemorrhagic stroke, and congestive heart failure.

Blood test: complete blood count, bleeding time and prothrombin time or partial thromboplastin time, glomerular filtration rates, total cholesterol, HDL and LDL cholesterol, and triglycerides. They were obtained from the last blood test carried out for the patient.

Use of accompanying medication: total number of drugs and anticoagulant type.

Consumption of “gastric protector” or nonsteroidal anti-inflammatories.

Dietary habits: usual consumption of food rich in vitamin K, alcohol consumption, and frequent diet transgressions.

### Primary outcome measure

Time on INR therapeutic levels in the last 6 months of receiving VKA treatment: Appropriate INR level controls will be assessed in two ways: measuring the therapeutic INR value percentages or measuring time percentages in therapeutic values estimated using the Rosendaal method [time frame, 0 and 6 months]

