## Abstract

**Background:**

Oral anticoagulant drugs represent an essential tool in the prevention of thromboembolic events. The ones in widespread use are vitamin K antagonists, whose plasma level is monitored by measuring prothrombin time using the international normalized ratio. If its values are out of the recommended range, the patient will have a higher risk of suffering from thromboembolic or hemorrhagic complications. Previous research has shown that approximately 33% of patients keep having values at an inappropriate level. The purpose of the proposed study is to improve the international normalized ratio control results by a joint didactic intervention based on the Junta de Andalucía School for Patients method that will be implemented by anticoagulated patients themselves.

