**Methods:**

A randomized controlled trial will be undertaken at primary care centers from one healthcare area in Málaga (Andalusia, Spain). Study population: patients participating in an oral anticoagulant therapy program of vitamin K antagonists.

First step: identification of patients in the oral anticoagulation therapy program with international normalized ratio control of the therapeutic level at 65% or less over total time. Second step: patients with international normalized ratio (INR) control figures under 2 or above 3 will be assigned to two different groups:

Group 1 or joint intervention group: patients will be instructed in the joint didactic “from peer to peer,” by a previously trained and expert anticoagulant patient.

Group 2 or control group: the control group will receive the usual clinical practice. They will be evaluated by nurses about once a month, except for cases in which their INR figures are under 2 or above 3, and those patients will be evaluated more frequently.

A total of 312 individuals will be required (156 in each group) to detect differences in INR figures equal to or higher than 15% between the groups.

Study variables: time on therapeutic levels before and after the intervention; sociodemographic variables; vital signs; the existence of cardiovascular risk factors or accompanying diseases in the clinical records; laboratory test including complete blood counts, bleeding time, and prothrombin time or partial thromboplastin time; and blood chemistry, other prescribed drugs, and social support.

A quasi-experimental analytic study with before-after statistical analysis of the intervention will be conducted. Linear regression models will be applied for the main variable results (international normalized ratio value, time on therapeutic level) inputting sociodemographic variables, accompanying diseases, and social support.

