### Aim

The present study aims to show that conducting an organized group educational intervention on VKA-anticoagulated patients by using the Junta de Andalucía School for Patients method will result in reductions in inappropriate INR control levels.

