#### Step I

Considering that the prevalence of patients on AOT is about 1.5% of the general population, it can be claimed that the target population to initiate our study will be 750 anticoagulated patients (using anticoagulant drug consumption data from our health área in Málaga, Spain). Prior studies indicated [15–17] that at least 33% of these patients would not have an appropriate INR control level (INR values above 2 and under 3 or under 3.5 for prosthetic valve wearers). To reach an appropriate sample size in the estimated proportion, the following terms must be considered: (1) using a normal asymptotic confidence interval with a correction to finite populations on bilaterally of 95%, (2) assuming that the expected population is approximately 33%, and (3) since the population total size is 750, it was deemed necessary to include 312 experimental units in this study (Fig. 1).

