#### Step II

Accepting an alfa risk of 0.05 and a beta risk of 0.20 in a bilateral comparison between the study group and the control group, 312 individuals will be required (156 in each group) to detect differences in INR figures equal or higher than 15% between the groups for the primary target. It has been estimated by the researches that there will be a tracking loss rate of 10%. It will be assumed these lost individuals are impossible to locate or are those who do not wish to take part or cannot attend the scheduled revisions, in accordance with the study intervention plan, as well as deaths occurring within 6 months of the intervention. Given the relevant impact of the development of cardioembolic or hemorrhagic events due to out of range INR control values, changes of approximately 15% could have significant clinical relevance.

Patients will be recruited from the list of patients taking anticoagulant drugs included in the digital medical record according to the inclusion and exclusion criteria. The recruitment period will last for 1 month.

To reach the required sample size, all patients from the four health centers on AOT using vitamin K antagonists will be studied. Patients will be selected from their own PCC once identified by “Seguridad Social de Andalucia” user number (NUSSA). Once the inappropriate individuals are identified, they will be consecutively placed considering their social security number in every health center. After that, patients in each strate (PCC) will be randomly distributed in the intervention group or the control group. The investigators will try to avoid bias depending on each health center issues.

It has been estimated a follow-up loss ratio of approximately 10%. Deaths 6 months from the intervention, and inability to locate individuals, or not attending to the scheduled meetings will be considered as losses when dealing with the study intervention program.

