Every patient will be required to attend one group meeting (the intervention group). The control group will perform the usual clinical practice: people will be scheduled to visit with a nurse about once per month, except for cases in which controls are inappropriate who will be scheduled for more frequent visits. Patients in the control group will not attend any of the group sessions. Both groups will be followed with their usual INR controls, carrying out the needed number of measurements under the guidance of the health professionals involved in the appropriate INR control of all patients.

As the final step, once the intervention had been carried out for every indicated patient, INR figures and data will be collected over the next 6 months. The study participants will be able to withdraw their informed consent at any time, and they will be free to leave the study if they do not want to complete the 6 months of INR control after the educational intervention. The main reasons for discontinuing or modifying the interventions assigned to each study participant will be a withdrawal request, a participant’s death, or stopping the use of antivitamin K drugs. Unmasking will be allowed in those cases.

Protocol amendments will be reported to the research ethics committee and to the funding foundation (FIMABIS) and trial sponsor ([name]).

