#### Second step

Once the study of the VKA anticoagulation control degree is performed, patients who present inappropriate control values will be selected. A list of patients with deficient INR control at the participant health centers will be made. An inappropriate INR control is defined as when the therapeutic INR values (range from 2 to 3, or to 3.5 in prosthetic valve wearers) percentages (TRT) are less than 65%, using the Rosendaal method to obtain them. In cases of no availability, INR controls will be considered inappropriate when the therapeutic INR value percentage results are less than 60% of the total measures. For any of the assumptions, the assessment period is at least the last 6 months. There is no anticipated harm and compensation for trial participation. As a provision for post-trial care, patients on inappropriate INR control figures will be indicated to stop vitamin K antagonist intake. They will be indicated to start a non-vitamin K antagonist oral anticoagulant (NOAC) intake if they suffer from atrial fibrillation and anticoagulation criteria exist.

The data monitoring committee is composed of the main researcher ([name]) and doctors [name] and [name]. This committee is independent of the sponsor, and funding is not made under any term.

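### Valve patients are selected on an INR range that reads as 2 to 3.5 but scored for the primary outcome on 2.5 to 3.5, and continuous comparisons get a confidence interval only when significant

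*Protocol article*

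**What the plan says.** **Primary outcome.** Under Primary outcome measure, control is assessed by "measuring the therapeutic INR value percentages or measuring time percentages in therapeutic values estimated using the Rosendaal method", at 0 and 6 months. The range is set under Variables: operative definition: 2 to 3 for atrial fibrillation, and 2.5 to 3.5 for thromboembolism prevention after heart valve surgery.

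**Selection.** Second step defines inappropriate control as less than 65% in range by the Rosendaal method, or less than 60% of measurements where that is unavailable, over at least the last 6 months. The range there is "range from 2 to 3, or to 3.5 in prosthetic valve wearers". Step I uses the same form when it describes the share of patients without adequate control: "INR values above 2 and under 3 or under 3.5 for prosthetic valve wearers". Both change the upper limit for valve patients and leave the lower limit at 2. The bullet in the inclusion criteria (under 2 or above 3) makes no exception for valves.

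**Intervals.** Statistical analysis gives odds ratios with 95% confidence intervals for two-way tables. For the comparisons of continuous variables, it says that 95% intervals will be calculated when the result is statistically significant.

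**Direction of deviation.** The abstract links out-of-range INR to two kinds of harm: "If its values are out of the recommended range, the patient will have a higher risk of suffering from thromboembolic or hemorrhagic complications". Step II does the same: "Given the relevant impact of the development of cardioembolic or hemorrhagic events due to out of range INR control values". The list under Secondary outcome measures has no comparison of time above range or time below range.

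**The concern.** The therapeutic range is part of the definition of the primary outcome, because a change in a limit changes every patient's percentage. Eligibility and the baseline value come from the same 6 months of INR readings before the intervention. As written, a valve patient's readings are judged on 2 to 3.5 when deciding entry and on 2.5 to 3.5 when recording the outcome. Readings between 2 and 2.5 count as in range for the first purpose and below range for the second.

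Two things are at stake for this subgroup. One is who enters: a patient who falls under 65% on 2.5 to 3.5 may not on 2 to 3.5, and so is left out of a trial meant for poorly controlled patients. The other is what the primary percentage means, including how large a given change in INR appears.

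The interval rule adds a separate problem. Without a significant result, the plan promises a p-value and no interval for the primary comparison. The reader then cannot see which differences the data exclude.

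**Working it through.** **1. The limits side by side, for valve patients**

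| Section | Use | Lower | Upper |
|---|---|---|---|
| Step I | share not adequately controlled | 2 (as it reads) | 3.5 |
| Second step | eligibility | 2 (as it reads) | 3.5 |
| Variables: operative definition | primary outcome | 2.5 | 3.5 |

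The upper limit agrees throughout. Only the lower limit conflicts, and it moves the percentage in range and the percentage below range by the same amount.

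**2. Size of the conflict**

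The article gives no INR distribution. Assume a valve patient's INR is normal with mean 2.8 and SD 0.8. Percentage in range = Φ((upper − 2.8)/0.8) − Φ((lower − 2.8)/0.8).

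- Below 3.5: Φ(0.875) = 80.92%
- Below 2: Φ(−1) = 15.87%
- Below 2.5: Φ(−0.375) = 35.38%
- In range, 2 to 3.5: 80.92 − 15.87 = 65.05%, about 65%
- In range, 2.5 to 3.5: 80.92 − 35.38 = 45.54%, about 45.5%
- Gap: 35.38 − 15.87 = 19.5 points

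This patient just misses the under-65% rule on 2 to 3.5 and meets it easily on 2.5 to 3.5.

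Range of the gap, Φ((2.5 − mean)/SD) − Φ((2 − mean)/SD):

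- mean 2.5, SD 0.6: 50.0 − 20.2 = 29.8 points
- mean 3.0, SD 1.0: 30.9 − 15.9 = 15.0 points
- other combinations of mean 2.5 to 3.0 and SD 0.6 to 1.0 lie between these.

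**3. What it does to a treatment difference**

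An added illustration: a valve patient's mean INR rises from 2.5 to 2.8, with SD 0.8.

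- On 2 to 3.5: at mean 2.5, Φ(1.25) − Φ(−0.625) = 89.44 − 26.60 = 62.84%. Change: 65.05 − 62.84 = +2.2 points.
- On 2.5 to 3.5: at mean 2.5, Φ(1.25) − Φ(0) = 89.44 − 50.00 = 39.44%. Change: 45.54 − 39.44 = +6.1 points.

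The same change in INR scores 3.9 points differently (6.1 − 2.2). Over the whole trial this is multiplied by the share of valve patients. At an assumed share of 10% it is 0.1 × 3.9 = 0.4 points on the between-arm difference, and at 30% it is 1.2 points. The shift in the level of each arm would be 0.1 × 19.5 = 2.0 points and 0.3 × 19.5 = 5.9 points.

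**4. What a missing interval would hide**

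Step II plans 156 per arm and 10% loss: 156 × 0.9 ≈ 140. For an assumed SD of 20 to 30 points, the 95% half-width is 1.96 × SD × √(2/140):

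- SD 20: 4.7 points
- SD 30: 7.0 points

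A non-significant difference lies within one half-width of zero, so its interval reaches at most two half-widths from zero: 9.4 to 14.1 points. If the 15% in Step II means 15 percentage points, a null result under these assumptions would exclude the target difference. Without the interval, the report would not show this.

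**The case against.** **The lower limit may be shorthand.** The authors may have meant 2.5 to 3.5 throughout and named only the limit they thought worth mentioning. That is possible, and the fix is then only an edit. But the two sentences as printed leave 2 in place, and the people who draw up the list of eligible patients will apply what is printed.

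**The effect on the trial result may be small.** This stands. The conflict concerns valve patients only, and step 3 of the working puts the effect on the between-arm difference at around a point for the shares assumed there.

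**Stronger readings that a reader might infer, and that the documents do not support:**

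- *That the comparison between arms is biased.* Patients are randomized within each health center, and nothing suggests that the arms are scored on different ranges. The conflict affects who enters and what the percentage means, not the balance between arms.
- *That baseline and 6 months are scored on different ranges, so that valve patients show a false fall of 19.5 points.* The article defines the outcome once for both times. The fix should rule this out, but the text does not state it.
- *That leaving out time above and below range is an error.* An in-range percentage fits the aim that the program "will result in reductions in inappropriate INR control levels". A split of out-of-range time is a derived summary that an analysis plan commonly specifies. Direction is also partly covered, since the abstract says "Linear regression models will be applied for the main variable results (international normalized ratio value, time on therapeutic level", and stroke diagnoses are listed as secondary outcomes. The documents do not say which way INR will move.
- *That no null result would carry an interval.* Odds ratios for two-way tables get one whatever the p-value. The gap is in continuous comparisons, which include the primary outcome.

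**Conclusion.** The valve range is contradictory within the article. The selection text reads as 2 to 3.5, and the outcome definition says 2.5 to 3.5. Under an assumed normal INR with mean 2.8 and SD 0.8, that is about 65% against 45.5% of time in range: 19.5 points, or 15 to 30 over means of 2.5 to 3.0 and SDs of 0.6 to 1.0. It touches both the primary outcome and the under-65% entry rule, but only for valve patients. Because the article does not give their number, the effect on the whole trial cannot be fixed.

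The interval rule for continuous comparisons is also badly set, because it withholds the estimate's precision exactly when the test is not significant.

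The absence of separate outcomes for time above and below range is not an error. Adding them is a matter of choice.

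**What to change.** 1. **State one valve range.** Use 2.5 to 3.5 as in Variables: operative definition, or 2 to 3.5 if that is what the clinicians use. Apply it to eligibility, the baseline value and the 6-month primary outcome, and align Step I, Second step and the inclusion bullet. If patients were already selected under 2 to 3.5, keep them in the trial and report how many would be classified differently.
2. **Replace the interval rule.** Report the between-arm difference with a 95% confidence interval whatever the p-value, starting with the primary outcome.
3. **Optional.** Report percent time above and percent time below each patient's own range, descriptively and with 95% intervals. The data are already planned: "INR figures and data will be collected over the next 6 months". With 140 per arm and an SD of 20 to 30 points, the half-width is again 4.7 to 7.0 points, and power for a 5-point difference is only 55% to 29%. The absence of a difference would therefore not show safety.

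The cost is one decision on the valve range and a few lines of wording, with no new data, visits or patients.

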### Secondary outcome measures

2.Sociodemographic: record of age and sex [time frame, start of the study]3.Body mass index (BMI): determination of the body mass index calculated as the weight measured in kilograms (kg) divided by the height measured in meters squared (weight/height^2^) (kg/m^2^) [time frame, 0 and 6 months]4.Diastolic and systolic blood pressure: determination of diastolic and systolic blood pressure measured in millimeters of mercury (mm/Hg), average of 2 determinations [time frame, 0 and 6 months]5.Heart rate: determination of the number of heartbeats per minute, average of 2 determinations [time frame, 0 and 6 months]6.Smoking habit: incidence of smoker’s habit status in the electronic medical record [time frame, 0 and 6 months]7.Diabetes: incidence of the condition of diabetes in the electronic medical record [time frame, 0 and 6 months]8.Arterial hypertension: incidence of the diagnosis of hypertension in the electronic medical record [time frame, 0 and 6 months]9.Dyslipidemia: incidence of the diagnosis of dyslipidemia in the electronic medical record [time frame, 0 and 6 months]10.Chronic renal failure: incidence of the diagnosis of chronic renal failure in the electronic medical record [time frame, 0 and 6 months]11.Atrial fibrillation: incidence of the diagnosis of atrial fibrillation in the electronic medical record [time frame, 0 and 6 months]12.Interventional cardiac valve diseases with or without atrial fibrillation: incidence of the diagnosis of interventional cardiac valve diseases in the electronic medical record [time frame, 0 and 6 months]13.Ischemic cardiopathy: incidence of the diagnosis of ischemic cardiopathy in the electronic medical record [time frame, 0 and 6 months]14.Thromboembolic disease history (stroke, transient ischemic attack): incidence of a thromboembolic disease history (stroke, transient ischemic attack) in the electronic medical record [time frame, 0 and 6 months]15.Hemorrhagic stroke: incidence of the diagnosis of hemorrhagic stroke in the electronic medical records [time frame, 0 and 6 months]16.Congestive heart failure: incidence of the diagnosis of congestive heart failure in the electronic medical records [time frame, 0 and 6 months]17.Glomerular filtration rates: determination of the total glomerular filtration rates in ml/min/1.73 m^2^; change from basal to 12 months [time frame, 0 and 6 months]18.Total cholesterol: determination of total cholesterol measured in milligrams per deciliter (mg/dl); change from basal to 12 months [time frame, − 6 and 6 months]19.HDL cholesterol: determination of high-density lipoprotein cholesterol (HDLc); LDLc measured in milligrams per deciliter (mg/dl) (low-density lipoprotein cholesterol); HDLc measured in milligrams per deciliter (mg/dl); change from basal to 6 months [time frame, − 6 and 6 months]20.LDL cholesterol: determination of low-density lipoprotein cholesterol (LDLc); LDLc measured in milligrams per deciliter (mg/dl); change from basal to 6 months [time frame − 6 and 6 months]21.Triglycerides: determination of total triglycerides measured in milligrams per deciliter (mg/dl); change from basal to 12 months [time frame, − 6 and 6 months]22.Total number of drugs: determination of the total number of different medications prescribed in the electronic medical records; change from basal to 12 months [time frame, − 6 and 6 months]23.Anticoagulant type: determination of the anticoagulant type prescribed in the electronic medical records; change at baseline and at 12 months [time frame, − 6 and 6 months]24.Consumption of “gastric protector”: determination of the consumption of “gastric protector” prescribed in the electronic medical records; change at baseline and at 12 months [time frame − 6 and 6 months]25.Usual consumption of food rich in vitamin K: change in usual consumption of food rich in vitamin K; change at baseline at 12 months [time frame, − 6 and 6 months]26.Alcohol consumption: change in usual alcohol consumption; change at baseline and at 12 months [time frame, − 6 and 6 months]27.Eligibility: minimum age, 18 years; sex, all; accepts healthy volunteers, no

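### The stroke outcomes record standing status rather than new events, and deaths count as losses, so the arms cannot be compared completely on new harm

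*Protocol article*

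**What the plan says.** All references are to the protocol article.

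- **Secondary outcome measures, item 14** (thromboembolic disease): "incidence of a thromboembolic disease history (stroke, transient ischemic attack) in the electronic medical record [time frame, 0 and 6 months".
- **Secondary outcome measures, item 15**: "Hemorrhagic stroke: incidence of the diagnosis of hemorrhagic stroke in the electronic medical records [time frame, 0 and 6 months".
- **Same list, item 6**, in the same form of words: "incidence of smoker’s habit status in the electronic medical record [time frame, 0 and 6 months". Diabetes, hypertension and atrial fibrillation are worded alike.
- **Variables: operative definition** places thromboembolic history and hemorrhagic stroke among the covariates: "Independent variables, also called study variables, are those that could affect the result variables".
- **Step II** gives the reason for the 15% target: "Given the relevant impact of the development of cardioembolic or hemorrhagic events due to out of range INR control values". The Background also links variation of about 15% in control to clinical problems.
- **Step II** treats deaths as losses twice. The first time, the 10% loss allowance covers patients who cannot be found or do not attend "as well as deaths occurring within 6 months of the intervention". The second list of losses opens with "Deaths 6 months from the intervention, and inability to locate individuals".
- **Timetable and work program** plans a before-after comparison within each subject and a comparison between the arms.
- **Description of the intervention** names death as one reason for discontinuing and allows unmasking in such cases.

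**The concern.** A history of stroke, once in the record, stays there. Reading it at month 0 and month 6 shows who has ever had an event, whereas incidence means events that arise during follow-up. The two agree only for patients who start without the entry.

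The loss rule adds to this. A patient who dies of a stroke or a bleed joins those who moved away or did not attend, and no listed outcome is death or its cause. The list also has no item for bleeding outside the brain or for embolism and thrombosis other than stroke and TIA. The Background, however, names pulmonary embolism, deep vein thrombosis and prosthetic valves among the main reasons for treatment.

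At stake is the descriptive account of harm. The protocol argues that INR control matters because poor control leads to embolic and bleeding events. Readers will want to see those events by arm, and the printed definitions would supply an incomplete count under a label that promises a full one.

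**Working it through.** No stated figure decides this point, and the sample size of 312 is not in question here. The check is a reading of the definitions, followed by a rough size.

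**Step 1. What incidence means in this list.** The wording used for items 14 and 15 is also used for smoking status, diabetes and atrial fibrillation, which are standing conditions. The operative definitions list the two stroke items as factors that may influence the result. Together these point to presence in the record, not to new events.

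**Step 2. What the two readings can show for item 14.**

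| Month 0 | During follow-up | Month 6 | What is seen |
|---|---|---|---|
| No history | Nothing | No history | No change, correct |
| No history | First non-fatal stroke or TIA | History | Change, event seen |
| History | Nothing | History | No change, correct |
| History | Further non-fatal stroke or TIA | History | No change, event missed |
| Either | Fatal event | Counted as a loss | No outcome entry for death |
| Either | Bleed outside the brain, or venous or systemic embolism | No item | Not seen |

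Item 15 behaves in the same way for hemorrhagic stroke. The two items are separate, so a patient with an earlier stroke or TIA can still turn positive on item 15. Only recurrence of the same type is hidden.

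**Step 3. How the values would be compared.** The before-after comparison would bring out row 2 if each patient's two readings are paired. The Statistical analysis section names a paired test for continuous variables, and chi-square or Fisher's test for categorical ones. If the 6-month proportions alone are compared, old and new events are mixed.

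**Step 4. Size.** The prior-history share and the event rate are assumptions; the documents give neither.

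- Patients positive at the start, if 10% to 25% have a prior stroke or TIA: 0.10 × 312 = 31 to 0.25 × 312 = 78.
- New events in 6 months, at an assumed 1% to 6% per year: 312 × 0.5 × 0.01 = 1.6 to 312 × 0.5 × 0.06 = 9.4.
- If these were all stroke or TIA and risk did not depend on history, the hidden share equals the prior-history share: 1.56 × 0.10 = 0.2 to 9.36 × 0.25 = 2.3 events. If prior stroke raises risk, the hidden share is larger.
- Visible first events: from 1.56 × 0.75 = 1.2 to 9.36 × 0.90 = 8.4. A 6-month value read alone would set these against 31 to 78 standing histories.
- Losses: 10% of 312 is 31. Deaths are some unknown part of these.

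**The case against.** **Events are the rationale, not an objective.** The aim and the primary outcome concern INR control. Using clinical consequences to explain why 15% matters does not oblige a 6-month educational trial of 312 patients to count events, and the same items appear elsewhere as covariates. This stands as far as power and the primary analysis go. It does not rescue items printed as secondary outcomes under a label they cannot meet.

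**The arms can be compared.** A reader might infer that no comparison of new harm is possible, even descriptively, or that patients with a prior stroke or TIA contribute no information. The documents support neither. Two readings per patient and a planned before-after comparison reveal first non-fatal strokes, TIAs and hemorrhagic strokes by arm, and patients with a prior stroke or TIA can still convert on item 15.

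**Incidence may mean new events.** Taken literally, it would. The use of the same phrase for smoking status, and the word history in item 14, argue against that, though this is an inference from a loosely worded list.

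**Deaths are not invisible.** Death is named separately as a reason for discontinuing, so deaths should be identifiable by arm. That is fair. What remains is that Step II pools them with other losses and that no printed outcome reports them.

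**Other events may be on the collection forms.** The article mentions attached forms that are not shown, and these may hold bleeding or embolism items. The point about missing items is therefore weaker than the points about the printed definitions and the loss rule.

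**Risk from self-management.** A reader might also infer that the intervention adds danger by handing control to patients. The documents describe one educational session, with INR control in both arms left to health professionals as usual, so that argument is not made here.

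**Conclusion.** The point holds in a limited form. As printed, items 14 and 15 detect a first non-fatal event of each type and miss a recurrence of the same type, and a 6-month value read alone is not an incidence. Deaths within 6 months are pooled with non-location and non-attendance. No printed outcome covers death, extracranial bleeding or non-cerebral thromboembolism. New harm can therefore be compared between arms only incompletely.

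The number of hidden recurrences is probably small: about 0.2 to 2.3 under the assumed rates, and more if prior stroke raises risk. With so few events in total, each missed one matters to a descriptive count, but no test is at stake.

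It may be tempting to conclude that counting deaths as losses undermines the main result. The documents do not support that: a patient who dies cannot supply six months of INR values, so the primary comparison faces ordinary attrition and no more. The conclusion rests on reading the two items as status in the record, and on the shown text being the full outcome list.

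**What to change.** 1. Keep items 14 and 15 as baseline characteristics.
2. For follow-up, extract from the digital record new dated thromboembolic and bleeding events, at any site, first or recurrent, over the same 6-month window in both arms. Report them descriptively by randomised arm.
3. Report deaths by arm, with cause where recorded, separately from patients who were not located or did not attend. Amend both statements in Step II to match.

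The cost is a few dated fields on the collection sheet and slightly more extraction time from a record that staff already read. The primary outcome and the sample size do not change.
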